**Study 1**

***Time course of recovery of plasma arginine, NOS cofactors and pharmacodynamic measures in uncomplicated and severe malaria:*** Our data on existing cryopreserved plasma in Indonesian adults indicate that plasma arginine levels in severe malaria have returned to normal by day 3 (fig. 2), however the rate of recovery of arginine levels in uncomplicated and severe malaria is not known. In 20 patients with UF and 20 with SM (defined above), we will measure serial measurements of plasma arginine to determine the natural history of recovery of plasma arginine concentrations in patients with malaria, and the natural history of recovery of the pharmacodynamic measurements to be used in stage 2.

*Clinical measures.* Vital signs (pulse rate, BP, temperature, respiration rate), and a standardised clinical assessment (symptom/signs listed in Table footnotes) will be serially monitored over 24-72 hours (see table 1). ECG will also be monitored from 0-240 mins.

*Sampling regimen and amino acid measurements:*

1. Blood: An additional venous cannula for sampling will be placed at the time of enrolment. At the time of cannula insertion we will take 10ml heparinised baseline blood (processed as per enrolment in NO Study II SOP for heparinised blood).

Subsequent sampling regimens:

2 ml (in heparinised blood) collected on up to five further occasions over 48-72 hours depending on clinical need for hospitalisation (see example of sampling schedule in table 1). **Of particular note, for the pharmacokinetic-pharmacodynamic modeling proposed in studies 1 and 2, it is advantageous for serial blood samples/measures to be collected at varied time points.**

Total amount of blood taken: ≤20 ml.

Plasma will be cryopreserved at -70ºC for later quantitation of the following:

- arginine, its metabolites and related amino acids by HPLC25 (Shimadzu) using our established methodology (figure 2).
- NO metabolites (nitrate plus nitrite) using Greiss reagents as we have performed previously, and measures of oxidant production (including oxidized glutathione).
- CK, LFTs, lactate, urea, creatinine and the electrolytes required for study 2 below.
- sICAM-1 and other biochemical measures of endothelial activation

See footnotes to table 1 for where each test will be measured.

**Please see Appendix 2 for details of the type of specimens, type of tests and location of where the tests will be performed.**

2. Urine: will be collected on admission and whenever this is passed whilst in hospital for serial measures of NO and pterin metabolites. All urine collections, stabilization and processing will be done in dim light. Samples are not filtered or centrifuged because pterin species may be associated with particulate material in the urine43. Freshly obtained urine shielded from light will be separated into two samples: one for NO metabolites; the other for pterins which will immediately stabilized by acidification to pH 1 with one drop of 6 N HCl and then immediately frozen. Urines are later thawed at 40o C and processed for pterins. The oxidized samples are then frozen at -150 o C for storage until analysis by HPLC at MSHR, Darwin.

3. Exhaled NO*:* We will also measure serial exhaled NO online at up to 6 timepoints over 24-72 hours (see example in table 1), as per exhaled NO SOP (Appendix 4) using ATS Guidelines44 We will be using on-line measurements using the NIOX NO analyzer. The advantage of this apparatus is that all that is required is a simple blow into a mouthpiece, without complex instructions and without complex breath holding instructions etc.. This analyzer has recently been licenced by the US FDA for clinical use in asthmatics, including children as young as 4 years old.

**See Appendix 4 for the standard operating procedures for measurement of exhaled NO.**

4. Physiological measures:In both UF and SM we will also serially quantify those physiological measures that will be used to assess pharmacodynamic effects of arginine in studies 2 and 3: brachial artery dilatation, doppler evaluation of microvascular blood flow, gas transfer (DLCO), ECG and physiological deadspace .

*4.1 Non-invasive vascular studies:* As additional pharmacodynamic measures, we will also use non-invasive vascular sonography to assess the impairment during malaria of endothelial function by brachial artery dilatation45-48, peak reactive blood flow by Doppler assessment and finger plethysmography.

Nitric oxide production by endothelial cells can be assessed by monitoring brachial artery reactivity to ischemia-promoting stimuli such as an inflated blood pressure cuff to assess endothelial production of nitric oxide. A baseline study of brachial artery ultrasound will be performed with the arm in the supine position. Arterial diameter and flow velocity will be determined. A cuff will be placed over the forearm (between the elbow and hand), distal to the ultrasound probe. Measurements will be performed at rest. The cuff will be inflated to 250 mmHg for 4.5 minutes and then released. Further ultrasound measurements will be performed after cuff deflation, and after 15 minutes of rest. In addition, peak reactive blood flow (a measure of distal microvascular blood flow) will be estimated by Doppler analysis immediately after cuff release. Finger plethysmography can measure both pulse rate as well as endothelial function. It causes no discomfort and requires just the placement of a sensor on the finger (similar to a finger pulse oximeter).

These will be measured up to five times as per example in table 1, to assess serial changes (and a hypothesized improvement) in endothelial function following treatment of malaria.

These measures are not painful. A cuff *above* the elbow can be unpleasant, but the technique we will use involves cuff inflation *below* the elbow, between the elbow and hand: this does not cause pain. The subject may experience very minor discomfort during inflation of pressure cuffs during the studies. This discomfort will be transient and would not be worse than having blood pressure measurement in routine clinical practice.

*Rationale for brachial artery studies:* the brachial artery is not the target in severe malaria, but the endothelial cell is. The brachial artery studies allow us to non-invasively measure of two key *endothelial* functions that are impaired in severe malaria:

*1. Endothelial dysfunction:*80% of the brachial artery dilatation following cuff-release is due to nitric oxide production by endothelial cells in real time. In severe malaria, the endothelium of blood vessels is severely affected: endothelial function is impaired, the endothelium is activated and ICAM-1 and other endothelial receptors are significantly increased49. Parasitised red cells cytoadhere to endothelium in capillaries and post-capillary venules. We cannot measure endothelial NO function directly in capillaries and venules, but we can measure endothelial function in the brachial artery. There is no reason to think that endothelial cell impairment due to low arginine will be any different in the artery to the impairment in endothelial function from low arginine in the capillary or venule endothelium. Our hypothesis is that arginine will allow endothelial cells (arterial, capillary, and venules) to recover their ability to make NO. In has been shown *in vitro* that nitric oxide can reduce the amount of ICAM-1 expression and decrease adhesion of infected red blood cells to endothelial cells50. We can measure endothelial NO production directly with brachial artery dilatation technique. Measuring brachial artery dilatation will supplement our other indirect measures of nitric oxide and arginine in plasma and urine (total body NO), by giving us a real-time bedside measure of *endothelial* NO production45-48. There will be training in this technique to all investigators working on site in Timika.

In order to have sufficient power to compare admission values of exhaled NO, vascular studies and physiological deadspace among disease categories, we will also measure these parameters on admission only in an additional 30 UM, 30 SM subjects (giving a total of 50 admission values in each group). This total sample size is based on the numbers required in our earlier NO-malaria studies to show a significant difference in NOS activity and arginine among the same groups of patients. We hypothesise that in severe malaria the physiological values and exhaled NO will be more impaired than in UM. In order to compare these values between uncomplicated falciparum malaria (in which cytoadherence to vascular endothelium occurs) and uncomplicated vivax malaria (in which cytoadherence to vascular endothelium does not occur) we will also undertake admission measurements of vascular function (as above), exhaled NO and physiological deadspace in 50 patients with uncomplicated vivax (UV) malaria (defined as per UF above, except for any level of *P. vivax* parasitemia on thick film in the absence of mixed infection). We hypothesise that these parameters will be more impaired in UF than UV.

All subjects will be treated with standard antimalarial drugs (currently quinine) as per standard RSMM/Depkes practice/protocols. Height and weight will be documented in all subjects.

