**3. Rationale for the Arginine-NO studies:**

There is a need for novel adjunctive antidisease therapies to reduce the unacceptably high case-fatality of severe malaria (SM) further1,2. Irrespective of its cause, hypoargininemia likely limits NO production and is associated with death in cerebral malaria25. Our NO-arginine-malaria studies and the results of arginine trials in related diseases suggest that arginine may have potential for therapeutic use in malaria. L-arginine is commercially available as an off-patent product for human use, is inexpensive, and has been widely used worldwide with little toxicity despite supra-physiological intravenous dosing as a diagnostic pituitary function test and administration in other human diseases36 (see also “clinical use of arginine in humans” above). It is important to determine whether arginine administered to malaria patients increases NO production, reduces measures of oxidant stress and has physiological effects at the doses proposed: this has implications for understanding the pathophysiology of severe malaria, as well as therapeutic implications. Arginine pharmacokinetics have not yet been described in hypoargininemic states such as uncomplicated and severe malaria. Our proposed safety, pharmacokinetic-pharmacodynamic and efficacy studies in uncomplicated malaria will be the first steps in cautiously determining if exogenous arginine administration has therapeutic potential in malaria.

**4. Our aims** are to:

4.1 Determine the natural history of recovery of plasma arginine levels and our pharmacodynamic measurements in uncomplicated and severe malaria.

4.2 Determine the pharmacokinetics, pharmacodynamics and safety of L-arginine in uncomplicated malaria**.**

4.3 Determine preliminary effects on biomarkers of outcome in uncomplicated malaria.

4.4 Establish the relationship between malaria disease severity and those measures used to monitor pharmacodynamic effects: exhaled NO, plasma/urine NO metabolites, oxidant stress, brachial artery dilatation, doppler evaluation of microvascular blood flow, physiological deadspace.

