**Patients:**

*Study 1:*

*Uncomplicated falciparum malaria (UF)*:

Inclusion criteria:

1. age 18-60 years
2. *P. falciparum* parasitemia (1,000-100,000 parasites/ul).
3. Clinical syndrome consistent will malaria associated with documented fever (axillary temperature  38oC) or self-reported history of fever in the last 48 hours with no other cause present
4. Time of commencement of quinine known
5. An indication for hospital admission [eg relative cannot stay at home to look after them or supervise their treatment at home, one episode of vomiting (but not repeated episodes of vomiting)], but not having the warning signs or severe malaria criteria in “exclusion criteria” below
6. Informed consent obtained

Exclusion criteria:

1. pregnancy or lactation
2. mixed infection with *P. falciparum* and *P. vivax*
3. warning signs ofaltered mental state and inability to sit unaided
4. features of severe/complicated malaria2 (see “severe malaria” below)
5. diabetes
6. systolic BP <100 mmHg
7. serious underlying diseases (cardiac, hepatic, kidney and lung)
8. malnutrion
9. other infection
10. concurrent therapy/medication including: anti-TB, Asthma drugs.

All UF subjects will be treated with quinine as per standard RSMM practice. Height and weight will be documented in all subjects.

*Severe malaria (SM)*, defined by modified WHO criteria42:

Inclusion criteria:

1. age ≥ 18 years
2. Informed consent obtained
3. Time of commencement of quinine known
4. any level of *P. falciparum* parasitemia, and one or more of the following criteria:
   1. acute renal failure (creatinine >265umol/L)
   2. hyperbilirubinemia (total bilirubin > 50 umol/L) with either renal impairment (creatinine > 130umol/L) or parasitemia of >100,000 parasites/uL
   3. blackwater fever
   4. hyperparasitemia (>10% parasitised red cells)
   5. cerebral malaria (Glasgow coma score <11)
   6. Hypoglycemia
   7. Respiratory distress (RR>32)
   8. Acidosis: venous bicarbonate < 15 mmol/L.
   9. Shock: systolic BP <80 mmHg with cold peripheries

Exclusion criteria:

1. severe anemia (Hb <6 mg/dL) and
2. pregnancy or lactation.

Clinical care, and monitoring will be as per standard national, RSMM and WHO protocols2.

*Studies 2 and 3: Uncomplicated falciparum malaria (UF)*:

Inclusion criteria:

1. age 18-60 years
2. *P. falciparum* parasitemia (1,000-100,000 parasites/ul).

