In accordance with the 2003 MOU signed between Menzies School of Health Research and NIHRD, all specimens will be handled by the guidelines stipulated in that document. The attached “special agreement”sample MOU (with strict limitations on the use of samples) will be used when samples are sent to the lab of another organization (see appendix 5).

Appendix 3

Physiological Tests to be done and location of tests:

| Type of Specimen | Type of Tests | Location Of Tests |
| --- | --- | --- |
| Exhaled air | Exhaled Nitric Oxide using NIOX apparatus | RSMM-Timika |
| Exhaled air | Physiological Dead Space | RSMM-Timika |
| Exhaled air | Diffusing Capacity-DLCO to measure gas transfer in lungs | RSMM-Timika |
| Ultrasound imaging of forearm and finger | Endothelial Function Testing (NO-dependent) | RSMM-Timika |

Appendix 4

Standard Operating Procedure for Measuring Exhaled Nitric Oxide with the NIOX Analyzer in Accordance to ATS Guidelines

Steps

1. Explain to the patient the complete procedure in Bahasa Indonesian or English.
2. NIOX machine should already be turned on and running for greater than 4 hours.
3. Calibrate the NIOX if the last calibration was greater than 14 days.
4. Replace NIOX room air filter with a new filter for every patient. Filters are not to be reused.
5. Enter patient’s name, ID number, examiners name and any other comment in the NIOX
6. Select either the meter or balloon view
7. While seated or lying upright, patient exhales and then places NIOX filter in the mouth.
8. Inhale to total lung capacity over 2-3 seconds with NIOX filter in the mouth.
9. Patient exhales slowly and constantly keeping constant flow as measured by indicators on either the meter or balloon view.
10. Repeat until three valid measurements are obtained for analysis.

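### The admission comparison of severe with uncomplicated falciparum malaria in Study 1 is confounded by unequal entry criteria and, for exhaled NO, will be selectively incomplete

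*Combined protocol and SAP*

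**What the plan says.** Aim 4.4 is to "Establish the relationship between malaria disease severity and those measures used to monitor pharmacodynamic effects". The paragraphs that close Study 1 supply the data. To the 20 UF and 20 SM patients followed serially they add an "additional 30 UM, 30 SM subjects" measured on admission only, "giving a total of 50 admission values in each group". (UM and UF are the same group: the Figure 1 legend defines UM as uncomplicated falciparum malaria.) The measures are exhaled NO, vascular studies and physiological deadspace. The justification is precedent: "This total sample size is based on the numbers required in our earlier NO-malaria studies", where the outcomes were NOS activity and arginine. The direction is stated: "We hypothesise that in severe malaria the physiological values and exhaled NO will be more impaired than in UM".

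The Patients section sets the entry rules. UF is age 18-60, with exclusions for diabetes, serious cardiac, hepatic, kidney or lung disease, malnutrition, other infection, and concurrent medication such as anti-TB and asthma drugs. SM is age 18 or over with two exclusions only: severe anaemia, and pregnancy or lactation. SM can be met by "cerebral malaria (Glasgow coma score <11"), by a respiratory rate above 32 or by shock, among other criteria.

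Appendix 4 describes the exhaled NO test. The patient sits or lies upright, empties the lungs, and then must "Inhale to total lung capacity over 2-3 seconds with NIOX filter in the mouth". A slow exhalation at constant flow against a visual indicator follows, repeated until three readings are valid. The Study 1 text presents the same test as a simple blow.

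The Study 1 Interpretation paragraph plans control for admission parasitaemia, age, sex and duration of fasting, but for serial recovery times. Nothing equivalent is stated for the admission values.

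**The concern.** Two separate problems meet in one comparison.

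First, the groups differ by design in ways that are not malaria severity. Older age, diabetes, vascular or lung disease, co-infection and asthma treatment can appear in SM and are kept out of UF. Several of these could plausibly affect vascular function, deadspace or exhaled NO whatever the severity of the malaria. The vivax group is defined by the UF rules, so the UF-vivax contrast is aligned on these points; the SM-UF contrast is not.

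Second, whether an exhaled NO value exists depends on how ill the patient is, and severity is the exposure under study. The extra 30 SM patients have no later visit at which a lost value could be replaced. The precedent studies measured NOS activity and arginine, which are blood assays needing no patient effort, so they carry no allowance for patients unable to perform. No alternative method, missing-value rule or over-recruitment is given.

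At stake is whether an SM-UF difference, or its absence, can be attributed to severity.

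**Working it through.** **The plan's figure.** 20 serial + 30 admission-only = 50 per group, which agrees. Its adequacy for power cannot be reproduced, because no alpha, power, effect size or SD is given. Below I assume two-sided 5% and 80% power, with differences in SD units.

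**Entry criteria side by side.**

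| | UF | SM |
|---|---|---|
| Lower age limit | 18 | 18 |
| Upper age limit | 60 | none |
| Pregnancy or lactation | excluded | excluded |
| Diabetes | excluded | not excluded |
| Serious cardiac, hepatic, kidney or lung disease | excluded | not excluded |
| Malnutrition | excluded | not excluded |
| Other infection | excluded | not excluded |
| Anti-TB, asthma drugs | excluded | not excluded |

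The adjustment planned for recovery times would cover age if extended to the admission values. Comorbidity, other infection and medication are in neither place.

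**Loss of exhaled NO values.** The share of SM patients unable to perform is not in the documents; I take 20-50%. Detectable difference ≈ (1.960 + 0.842) × √(1/50 + 1/n_SM). The two-sample t-test gives slightly larger values.

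| Unable (assumed) | SM values | Normal approximation | t-test |
|---|---|---|---|
| 0% | 50 | 2.802 × √0.0400 = 0.56 | 0.57 |
| 20% | 40 | 2.802 × √0.0450 = 0.59 | 0.60 |
| 30% | 35 | 2.802 × √0.0486 = 0.62 | 0.62 |
| 50% | 25 | 2.802 × √0.0600 = 0.69 | 0.70 |

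At a true difference of 0.56 SD, power falls from 80% to 75% with 20% missing and to 63% with 50% missing.

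**Selection.** Suppose the most severe fraction f of SM is untestable and severity correlates ρ with the measure (ρ = 0.3 to 0.5, assumed). The observed difference shrinks by ρ × φ(c)/(1 − f), where c is the normal quantile cutting off the top f.
- f = 0.2: φ(c)/(1 − f) = 0.280/0.8 = 0.350. The shrinkage is 0.105 to 0.175, so 0.56 becomes 0.46 to 0.39 SD and power is 57% to 44%.
- f = 0.5: 0.399/0.5 = 0.798. The shrinkage is 0.239 to 0.399, so 0.56 becomes 0.32 to 0.16 SD and power is 26% to 10%.

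Under these assumptions selection costs more than the lost numbers.

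**Confounding.** Suppose a share q of SM has a condition absent from UF by design that shifts the measure by s SD in the direction of impairment. The spurious difference is q × s. With q = 10-30% and s = 0.5-1.0 (both assumed) it is 0.05 to 0.30 SD. With 50 per group and no true difference, the chance of a significant result rises from 5% to between 6% and 32%.

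**The case against.** The strongest reply has four parts.

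- **No figure supports a large untestable share.** SM can be met through renal failure, jaundice with renal impairment or high parasitaemia, blackwater fever, hyperparasitaemia, hypoglycaemia or acidosis, none of which by itself prevents cooperation, and the test may be done lying upright. This stands. A reader might infer that many SM patients cannot do the test; the documents support only that some cannot.
- **The groups share some restrictions, and age was recognised as a confounder.** The lower age limit and the pregnancy exclusion are common to both, and the Interpretation paragraph controls for age, sex, parasitaemia and fasting. This stands as far as it goes, but the control is stated for recovery times and omits comorbidity and medication.
- **The breathing problem is confined to one test.** Brachial artery ultrasound needs no breathing manoeuvre. Gas transfer and plasma arginine or NOx are not among the measures named for the 50-patient comparison, so it is wrong to extend the argument to them. Nor can arginine or NOx serve as a fallback at this size: serial plasma sampling is specified for 20 per group, which detects about 0.91 SD on the same assumptions. All of this stands.
- **The loss of precision is modest at the lower end.** At 20% missing the detectable difference moves from 0.57 to 0.60 SD. This also stands; the stronger argument is bias, not precision.

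It is also fair that restricting SM to the UF criteria costs numbers and that some criteria are hard to apply at admission, such as pre-existing kidney disease against malarial renal failure. Restriction therefore belongs as a pre-specified additional analysis and need not be the main one.

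**Conclusion.** The concern holds. Followed as written, the plan gives an SM-UF contrast confounded by age above 60, comorbidity, other infection and medication, with no stated adjustment of the admission values. For exhaled NO it also gives fewer than 50 SM values, drawn from milder disease.

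The size rests on assumptions, because the documents give neither the untestable share nor the comorbidity mix. With 20-50% untestable, SM has 40-25 values and the detectable difference is 0.60-0.70 SD instead of 0.57 SD. Loss of the sickest patients would tend to shrink the exhaled NO difference; unmatched comorbidity may inflate differences. The net bias cannot be signed.

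A reader might go further and conclude that no result of this comparison could be read as an effect of severity. The documents do not support that. An exhaled NO difference seen despite attenuation would not be explained by the missing values, and brachial dilatation is free of the breathing problem; for both, what remains is the confounding, which can be reduced. The point concerns an observational aim and does not touch the randomised comparison in Study 3.

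**What to change.** 1. **Exhaled NO.** State 50 as the number of SM patients enrolled and report the number of valid values. Tabulate patients unable to perform by SM criterion, and limit the exhaled NO conclusion to SM patients able to perform. Use brachial artery dilatation, planned for all 50, as the anchor for the severity comparison. Recruiting until 50 valid values are reached would need 50/0.8 = 63 to 50/0.5 = 100 SM patients under the assumed range, and would not remove the selection.
2. **Confounding.** Adjust the admission comparison for at least age, sex and hours since quinine; a known quinine start time is already an entry criterion in both groups. Record pre-existing comorbidity, other infection and medication at SM enrolment. Pre-specify a further analysis restricted to SM patients who meet the UF age, pre-existing-disease and medication criteria, worded so that renal or hepatic dysfunction caused by malaria does not exclude a patient.

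The cost is a few case report form fields and some analysis wording. The restricted SM subset will be smaller and less precise, and the claim for exhaled NO narrower.
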